##### Special restrictions for women

Current or planned pregnancy or nursing womenWomen of childbearing potential who are not using and not willing to use medically reliable methods of contraception for the entire study duration (such as oral, injectable or implantable contraceptives or intrauterine contraceptive devices), unless they are surgically sterilized and/or hysterectomized or there are any other criteria considered sufficiently reliable by the investigator in individual cases

#### Subject information and recruitment

If a patient appears to be eligible for the study, either the investigator responsible for that site or delegated medical doctors will provide the patient a full verbal explanation of the trial and the Patient Information Sheet so that the patient can consider participating. This will include detailed information about the rationale, design and personal implications of the study. After information is provided to patients, they will have sufficient time to consider participation before they are asked whether they would be willing to take part in the trial.

It is imperative that written consent be obtained before any trial-specific procedures commence. The investigator will then record the details of these trial patients in trial-specific lists.

#### Randomization and stratification

This trial is designed as an open-label trial. Randomization will be performed at the Institute for Medical Informatics, Biometry and Epidemiology (IBE) of the University of Munich, and the treating physicians will be informed about the treatment arm to which a patient is assigned.

Randomization to both treatment arms will be performed in a ratio of 1:1. The randomization technique is based on randomized, balanced blocks with random block length. The procedure considers stratification by type of surgical procedure (ileal conduit or neobladder). The IBE will provide an internet-based randomization tool (Randoulette), which chooses the colloid treatment group for a new patient fulfilling the eligibility criteria and having signed the informed consent. Randoulette will register the patient by the patient’s pseudonym or screening number, sex, year of birth and stratum (ileal conduit or neobladder) before the allocated colloid treatment group is provided.

### Statistical planning and analysis

#### Statistical analyses

The primary efficacy analysis statistically tests superiority of HA versus HES at an α significance level of 5 % (two-sided, simultaneously testing both sides at a level of 2.5 %) with respect to the primary endpoint.

The primary endpoint is expected to be non-normally distributed. After logarithm transformation, the primary endpoint may not be normally distributed. Thus, the corresponding statistical null hypothesis is the hypothesis that the distribution functions of the endpoint in the HA group and the HES group are equal and will be tested non-parametrically with the Mann-Whitney-Wilcoxon test to detect directed differences of the distributions. The Mann-Whitney-Wilcoxon test will be applied. The one-sided *p* value will be calculated, if possible, using Fisher’s exact test.

The primary endpoint adjusts in a specific way for the preoperative cystatin C values. At the planning stage, the Mann-Whitney-Wilcoxon test will be applied in the stratified version by type of surgical procedure (ileal conduit or neobladder). If adjustments of stratification are deemed necessary during the course of the trial, the trial protocol will be amended.

A fixed-sample design is planned. Changes of trial design, if necessary or advisable, resulting from an interim analysis without significance testing (no αspent) had to keep the prespecified significance level. In that case, the Brownian motion will be used for modeling the primary test statistic based on the accumulating data as a stochastic process (see next section).

The distributions will be described at all time points by median, minimum, maximum and quartiles separately for both the HES and HA groups.

The primary statistical analysis will be based on the intention-to-treat (ITT) principle.

Analysis of all secondary endpoints and of patient characteristics will be descriptive. Descriptive comparisons will be conducted with the *t* test or, in the case of deviations from the normal distribution, with the Mann-Whitney-Wilcoxon test, or with Fisher’s exact test in case of a binary outcome.

Safety data will be analyzed descriptively in the two groups at least every 12 months.

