#### Sensitivity analyses

After the primary ITT analysis, sensitivity analyses will follow per protocol or according to as-treated principles. In addition to the primary Mann-Whitney-Wilcoxon analysis, the Mann-Whitney-Wilcoxon test will be applied to the cystatin C values at day 90, and, assuming approximately normal distributions after log transformation (natural logarithm), explorative regression analyses will be performed modeling the log-transformed (natural logarithm) cystatin C values depending on treatment group, log-transformed (natural logarithm) baseline cystatin C values and other potentially prognostic factors.

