## Appendix

**Table 1 Tab1:** Flowchart

Schedule of activities	Visit 1	Visit 2	Visit 3	Visit 4	Visit 5
	Screening day (day −1)	Day 0 (day of surgery)	Day 1	Day 3	Day 90
Informed consent	X				
Inclusion and exclusion criteria	X				
Demographic data	X				
Medical history (primary diagnosis)	X				
Pregnancy test for women of childbearing potential	X				
Mini Mental State Examination	X				
Life Quality Assessment (ADL, IADL)	X				X
Concomitant medications (diuretics)	X	X	X	X	X
Cystatin C, GFR, serum creatinine	X	X	X	X	X
ROTEM, Multiplate, PFA 100		X			
Randomization		X			
NGAL, syndecan 1, hyaluronan		X	X	X	
Study drug		X	X	X	
Blood products		X	X	X	
IV fluid amount		X	X	X	
Blood losses and urine output		X	X	X	
Nursing Delirium Screening Scale		X	X	X	
AEs and SAEs		X	X	X	X
Pruritus assessment					X

*ADL* activities of daily living, *AE* adverse event, *IADL* instrumental activities of daily living, *IV* intravenous, *NGAL* neutrophil gelatinase-associated lipocalin, *PFA 100* Platelet Function Analyzer 100, *ROTEM* rotational thrombelastometry, *SAE* serious adverse event2

**Table 2 Tab2:** Algorithm of infusions and transfusion in the operating room and intensive care unit

Hemodynamics	
ASA I and II patients without cardiac diseases or cerebral insufficiency:	
Stroke volume variation (SVV) <12 %	
Cardiac index (CI) > 2.5 L/min/m^2^	
MAD >60 mmHg	
ASA III and IV patients or patients with cardiac diseases or cerebral insufficiency:	
SVV <12 %	
CI >2.5 L/min/m^2^	
MAD >70 mmHg	
Central venous oxygen saturation >70 % or mixed venous oxygen saturation >65 %	
To reach the desired parameter:	
Start with infusion protocol (see below)	
If not successful within 15 minutes:	
Start with norepinephrine as first-choice vasopressor	
Infusion protocol	
Replacement of urine output with Ringer’s acetate solution in a 1:1 ratio	
Additionally, 500 ml of crystalloids for insensible sweating	
Replacement of blood and protein losses dependent on treatment assignment, with either HA 5 % or HES 6 % in a 1:1 ratio up to a transfusion trigger point or a maximum of 50 ml/kg/day	
Additionally up to 1500 ml of colloids for the protein loss into the third compartment

**Table 3 Tab3:** Transfusion protocol (in support of [24])

Red blood cells			
Hb (g/dl)	Risk factors	Transfusion	Evidence level
<6 g/dl	–	Yes	1c+
>6–8 g/dl	Adequate compensation, no risk factors	No	1c+
	Limited compensation or risk factors (cardiac diseases, cerebrovascular insufficiency)	Yes	1c+

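### No pre-treatment sample of syndecan 1, hyaluronan or NGAL is assured and no baseline-adjusted analysis is described for them: a cheap improvement to descriptive secondary endpoints

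*Protocol article*

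**What the plan says.** **Sampling (Appendix, Table 1).** The row "NGAL, syndecan 1, hyaluronan" is marked at Visits 2, 3 and 4 only (days 0, 1 and 3). Visit 2 is headed "Day 0 (day of surgery)", and randomization and study drug are first marked there. The row "Cystatin C, GFR, serum creatinine" is marked at all five visits, including the screening visit on day −1.

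**Endpoints (Secondary endpoints).** The glycocalyx markers are listed at days 0, 1 and 3, and NGAL at days 0, 1, 3 and 90. No change, ratio or reference value is attached to either. In the same list the GFR endpoint is a change relative to the start.

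**Analysis (Statistical analyses; Sensitivity analyses).** Of the primary endpoint the article says "The primary endpoint adjusts in a specific way for the preoperative cystatin C values". Of the secondary endpoints it says "Analysis of all secondary endpoints and of patient characteristics will be descriptive", and then "Descriptive comparisons will be conducted with the *t* test or, in the case of deviations from the normal distribution, with the Mann-Whitney-Wilcoxon test". The only model with a baseline covariate is for cystatin C: "explorative regression analyses will be performed modeling the log-transformed (natural logarithm) cystatin C values depending on treatment group".

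**The concern.** Shedding is a rise from a starting level, so it takes a value from before the exposure to measure it in a patient. The schedule assures such a value for cystatin C and creatinine but not for the glycocalyx markers or NGAL.

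Visit 2 cannot simply be read as preoperative. Blood loss and intravenous fluid are recorded there, and the delirium scale marked at that visit is, under Further objectives and variables, first given in the recovery room. The visit runs from before treatment to after surgery, and the marker draw could fall anywhere in it.

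Either position leaves something to settle:

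- If the draw follows the start of colloid, there is no baseline.
- If it precedes colloid, day 0 is listed as an outcome time at which the arms can differ only by chance, and nothing shown uses that value when days 1 and 3 are analysed.

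At stake is the trial's evidence on mechanism. The Background gives protection of the glycocalyx as the explanation for a benefit of albumin, and the Abstract names shedding among the secondary objectives.

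**Working it through.** **1. The plan's own sample size.** From Power considerations and sample size calculation: GFR factor 1.2, exponent −1.333, SD 0.2222, two-sided 5 %, power 80 %, dropout 10 %.

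- Difference in log cystatin C = ln(1.2)/1.333 = 0.1368.
- P = Φ(0.1368/(0.2222 × √2)) = 0.6683.
- Noether formula: total N = (1.960 + 0.842)²/(3 × (0.6683 − 0.5)²) = 92.4, so 46.2 per group, rounded up to 47. Power at 47 per group is 80.7 %.
- Enrolment: 94/0.9 = 104.4, rounded up to 105.

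These figures reproduce. No figure is given for the markers, so 47 assessed patients per arm is used below.

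**2. Is the comparison between arms valid without a baseline?** Yes. The article states "Randomization to both treatment arms will be performed in a ratio of 1:1", so starting levels balance in expectation. In simulation (47 per arm, normal data, 20,000 trials per setting), a Mann-Whitney-Wilcoxon test on levels alone had a type I error of 4.6 % to 5.0 %. The mean estimate of a true 0.5 SD effect was 0.50 SD at each correlation tried.

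**3. Chance imbalance in starting level.** The standard error of the arm difference is √(2/47) = 0.206 SD, a 95 % range of ±1.96 × 0.206 = ±0.40 SD. The difference exceeds 0.2 SD in 2 × (1 − Φ(0.2/0.206)) = 33 % of trials. Without a pre-colloid sample it can be neither seen nor corrected.

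**4. Precision.** Let ρ be the correlation between starting and later log marker levels. The document does not give it, so the values below are assumptions. Relative to comparing levels alone, the variance of the arm contrast is 1 − ρ² with baseline as a covariate (ANCOVA), and 2(1 − ρ) for change scores with equal SDs. The difference detectable with 80 % power on levels alone is 2.802 × 0.206 = 0.578 SD; the other columns multiply this by the square root of the variance ratio.

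| Assumed ρ | ANCOVA variance | Variance removed | Equivalent n per arm, 47/(1 − ρ²) | Change-score variance | Detectable, ANCOVA (SD) | Detectable, change (SD) |
|---|---|---|---|---|---|---|
| 0.3 | 0.91 | 9 % | 51.6 | 1.40 | 0.551 | 0.684 |
| 0.5 | 0.75 | 25 % | 62.7 | 1.00 | 0.500 | 0.578 |
| 0.7 | 0.51 | 49 % | 92.2 | 0.60 | 0.413 | 0.448 |

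Simulated power for a 0.5 SD effect was about 65 % on levels alone. With ANCOVA it was 71 %, 79 % and 92 % at ρ = 0.3, 0.5 and 0.7. With change scores it was 50 %, 65 % and 86 %. Change scores are therefore worse than levels alone when ρ is below 0.5; ANCOVA was better than both at each value tried.

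**5. NGAL at day 90.** The Secondary endpoints list includes it. The Table 1 row has no mark at Visit 5.

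**The case against.** The article does not say that raw levels will be compared. It names tests, not the quantity tested. The same sentence covers the GFR endpoint, which is a relative change, so the tests are compatible with change or ratio data. Day 0 may well be a pre-incision draw, and both its timing and the analysed quantity could stand in the full protocol or an analysis plan that is not shown. The endpoints are descriptive, and ANCOVA would gain precision for almost any continuous outcome. All of that stands, and it limits the point to an improvement.

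Three stronger readings are tempting and are not supported:

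- *The plan compares raw levels.* This is an inference from the endpoint wording and the named tests; the text is silent.
- *A colloid effect cannot be separated from starting levels.* Between arms this is wrong, because allocation is randomized (step 2). It can apply only to the rise within a patient, and only if day 0 follows colloid.
- *Day 0 mixes draws from before and after infusion.* Nothing in the article suggests that timing varies between patients. The order is just not given.

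The objection does not dispose of one matter. An analysis plan can choose a covariate later, but it cannot supply a sample that was not drawn in time. The printed schedule is detailed enough to show a screening sample for the renal markers and none for these.

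**Conclusion.** The point holds as a low-cost improvement to descriptive secondary endpoints. It is not a validity failure, and the primary endpoint and its conclusion are untouched.

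As printed, no pre-treatment sample of syndecan 1, hyaluronan or NGAL is assured, and no baseline-relative or baseline-adjusted analysis is described for them. The comparison between arms remains unbiased. What may be lost is the ability to measure shedding as a rise within a patient, the means to detect and adjust for chance imbalance (above 0.2 SD in a third of trials of this size), and 9 % to 49 % of the variance of the contrast for ρ from 0.3 to 0.7. That range rests on assumed correlations, 47 assessed patients per arm and approximately normal log marker levels. The day-90 NGAL mismatch is a separate inconsistency within the document and depends on none of these assumptions.

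**What to change.** 1. State in Table 1 that the day-0 sample for the three markers is drawn before the first study colloid, and treat it as baseline, not as an outcome time. If day 0 is meant as an end-of-surgery value, assay the baseline from the Visit 1 blood draw that already supplies cystatin C.
2. Analyse the later days by regression of the log marker on arm and log baseline marker, not by change scores. Use day 0 as the covariate only if it precedes colloid; a value taken afterwards may already carry part of the treatment effect.
3. Reconcile NGAL at day 90 between the Secondary endpoints list and Table 1.

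The first option costs one line in the table and a sentence of analysis text, with no extra samples, but gives up an immediate postoperative value. The Visit 1 option keeps that value at the price of one more assay set per patient.

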#### Secondary endpoints

Incidence of acute kidney injury as defined by RIFLE criteria (in hospital and at midterm [3 months]) (see Appendix: Table 4)Relative change of calculated GFR (by cystatin C) up to the third postoperative dayGlycocalyx shedding (syndecan 1, hyaluronan) at days 0, 1 and 3Glomerular damage as measured by neutrophil gelatinase-associated lipocalin at days 0, 1, 3 and 90Length of ICU and hospital stayNecessity and duration of renal replacement therapyPresence of pruritus at day 90

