## Methods/Design

In this single-center, open-label, randomized, comparative trial, we will investigate two parallel patient groups, comparing HA (test drug) versus HES (comparator). Ethical approval of this trial was obtained from the ethics committee of the Ludwig Maximilians University of Munich (reference number 311-11). The confirmatory statistical analysis is based on a leading surrogate parameter of renal function, with the aim of establishing a recommendation for therapy optimization. Because both investigational medicinal products (IMPs) are licensed for volume replacement in the perioperative setting in this trial, it is a phase IV trial. However, the clinical aim corresponds to that of a confirmatory phase IIb or III trial.

Randomization will be performed by stratifying participants by type of surgical procedure (ileum conduit or neobladder) to balance allocation to treatment groups with respect to this risk factor for postoperative renal dysfunction.

After randomization, each patient will receive the allocated volume replacement treatment according to the current prescribing information up to the seventh operative day. The patient should be kept on the allocated infusion solution during the first 90 days after operation if further volume replacement therapy becomes necessary, if not contraindicated, and if manageable.

A detailed schedule of study activities, and the treatment algorithm to be used for fluid management in both treatment arms are provided in the Appendix: Tables 1, 2 and 3.

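### Secondary comparisons, including the renal ones, ignore the surgical stratum used for randomisation and for the primary test; where that stratum is prognostic they are somewhat conservative (minor, free to improve)

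*Protocol article*

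**What the plan says.** All references are to the protocol article.

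- **Design.** Methods/Design stratifies randomisation by type of surgical procedure "to balance allocation to treatment groups with respect to this risk factor for postoperative renal dysfunction". Randomization and stratification repeats the stratum and adds: "Randomization to both treatment arms will be performed in a ratio of 1:1".
- **Primary test.** Under Statistical analyses, the Mann-Whitney-Wilcoxon test "will be applied in the stratified version by type of surgical procedure".
- **Secondary endpoints.** The same section states: "Analysis of all secondary endpoints and of patient characteristics will be descriptive". It then names the comparisons: a t test, or, "in the case of deviations from the normal distribution, with the Mann-Whitney-Wilcoxon test", or Fisher's "exact test in case of a binary outcome". No stratum is attached to any of them.
- **Renal secondary endpoints.** The list includes "Incidence of acute kidney injury as defined by RIFLE criteria" (in hospital and at 3 months), the relative change in calculated GFR to day 3, NGAL, and renal replacement therapy.
- **Other adjusted analysis.** Sensitivity analyses plans exploratory regression with potentially prognostic factors, but only for cystatin C values.

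**The concern.** The protocol gives a reason for stratifying: the type of urinary diversion affects renal outcome. It acts on that reason for the primary endpoint and drops it for the other renal endpoints, without explanation. The early GFR change shows this best. It is nearly the primary measure at an earlier time, yet it gets a t test or an unstratified rank test where the primary gets a stratified rank test.

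When a prognostic factor is balanced between arms by design, the treatment contrast no longer varies because of that factor. An analysis that ignores it still counts the between-strata variance as noise. The standard error is then too large, the true type I error falls below nominal, and power is lost. At stake is how the kidney injury and other renal results are read. The primary endpoint is a surrogate, and a conservative comparison of the clinical renal outcomes leans towards reporting no difference.

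**Working it through.** **1. The plan's own figure.** Inputs from Power considerations and sample size calculation: GFR factor 1.2, exponent -1.333, SD 0.2222, two-sided 5%, power 80%, dropout 10%.

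- Difference: ln(1.2)/1.333 = 0.1368.
- P = Φ(0.1368/(0.2222·√2)) = 0.6683.
- Noether: n per group = (1.960 + 0.842)²/(6·(0.6683 - 0.5)²) = 46.2, so 47 per group and 94 in total.
- 94/0.90 = 104.4, so 105 enrolled.

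Everything reproduces. The calculation concerns the primary endpoint only. No power or event rate is given for any secondary endpoint.

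**2. Continuous endpoints, analytically.** Let the stratum explain a share R² of the within-arm variance (assumed; not in the documents). The unadjusted test uses a standard error too large by 1/√(1 - R²). Its true size is 2Φ(-1.96/√(1 - R²)). If the adjusted test has 80% power, the unadjusted test has Φ((1.960 + 0.842)·√(1 - R²) - 1.960).

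| R² | True size | Power (adjusted = 80%) |
|---|---|---|
| 0 | 5.0% | 80.0% |
| 2% | 4.8% | 79.2% |
| 5% | 4.4% | 78.0% |
| 10% | 3.9% | 75.7% |
| 20% | 2.8% | 70.7% |

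With strata d within-stratum SDs apart and share p in one stratum, R² = d²p(1-p)/(1 + d²p(1-p)). For p = 0.5 and d = 1 this is 0.25/1.25 = 20%; for d = 0.5 it is 0.0625/1.0625 = 5.9%.

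**3. Continuous endpoints, simulated.** 47 per arm, effect 0.1368/0.2222 = 0.62 SD, 4,000 replicates, Mann-Whitney-Wilcoxon (MWW) against its stratified version (van Elteren):

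| Strata apart | Split | MWW power | van Elteren power | MWW size |
|---|---|---|---|---|
| 0 SD | 50:50 | 82.0% | 81.6% | 5.4% |
| 0.5 SD | 50:50 | 81.1% | 82.8% | 4.8% |
| 1 SD | 50:50 | 74.2% | 81.4% | 3.2% |
| 1 SD | 30:70 | 77.0% | 81.8% | 3.2% |

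A separate simulation with equal strata gave 72% against 79% at 1 SD and 79% against 80% at 0.5 SD.

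**4. Binary endpoints.** Fisher's test is exact and the Cochran-Mantel-Haenszel (CMH) test is asymptotic, so the cost of omitting strata has to be read like for like. Power with 94 patients, equal strata and treatment odds ratio 3:

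| Stratum risks | Fisher | Exact stratified | Chi-square | CMH |
|---|---|---|---|---|
| 20% / 20% | 60.0% | 59.4% | – | – |
| 20% / 40% | 60.9% | 63.4% | 68.7% | 70.5% |
| 15% / 50% | 50.5% | 58.9% | 59.7% | 67.4% |

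The gain from stratifying is about 0, 2 and 8 points. The last row implies a stratum odds ratio of (0.50/0.50)/(0.15/0.85) = 5.7. A second set of runs (baseline risk 15 to 30%, treatment odds ratio 0.3) compared Fisher with the exact stratified test. The gain was -0.3 to +0.9 points at stratum odds ratio 1, +0.2 to +2.2 at 2, and +2.8 to +4.0 at 4. Fisher's null rejection rate was already 2.2 to 3.1% at stratum odds ratio 1, which is discreteness and has nothing to do with strata.

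**5. Choice of test by normality.** A Shapiro-Wilk pre-test followed by t or MWW, 47 per arm, normal and lognormal data: type I error 4.8 to 5.1%. The choice makes the comparison neither conservative nor liberal here.

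**The case against.** The strongest reply is that these comparisons carry no claim. They are descriptive, no alpha or power is attached, the one confirmatory test is stratified, and the error runs towards too few rejections. That stands, and it is why the point is minor. It does not remove the point: significance tests are still named, and their p values will be read.

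A second reply is that this is detail for an analysis plan, and a fuller document may already name the strata. That may be so. But the article is not silent here. It states which tests will be used, in the section that stratifies the primary one.

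Third, the stratum is called a risk factor for renal dysfunction only. Nothing says it predicts pruritus, glycocalyx markers or length of stay, and a continuous endpoint unrelated to the stratum loses nothing. This stands, and the argument is strongest for the renal endpoints.

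Three stronger readings are tempting, and the documents do not support them:

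- A reader might infer that kidney injury by RIFLE is compared with a test picked after a normality check. Its incidence is binary and goes to Fisher's test by outcome type.
- A reader might infer that choosing between t and MWW by normality causes the conservatism. Step 5 shows that it does not.
- A reader might take the whole gap between Fisher and CMH (about 10 points at 20%/40%, about 17 at 15%/50%) as the price of ignoring strata. Much of it is exact against asymptotic testing, and preferring an exact test with about 47 per arm is defensible.

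**Conclusion.** The mismatch between design and analysis is real and its direction is known: where type of diversion is prognostic, the secondary comparisons as named are conservative and lose some power. For continuous endpoints the loss is about 1 to 2 points for a weak to moderate stratum effect (R² of 2 to 5%) and about 7 to 9 points for equal strata 1 SD apart (nearer 5 with a 30:70 split). It is nil with no stratum effect. For binary endpoints it is about 0 to 4 points like for like for stratum odds ratios up to 4, and about 8 only at 15% against 50% risk. Fisher's remaining conservatism is discreteness.

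All of these sizes rest on assumed stratum shares, stratum effects, treatment effects and event rates, because the documents give none for the secondary endpoints. The primary conclusion and the sample size are untouched. This is a free improvement of minor importance.

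**What to change.** In Statistical analyses, state that secondary comparisons are stratified by the randomisation stratum:

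- **Continuous endpoints:** the van Elteren test, or a linear model adjusted for the stratum.
- **Binary endpoints:** the Cochran-Mantel-Haenszel test, or its exact version when events are few, with a Mantel-Haenszel risk difference and 95% CI.
- **Every endpoint:** name the test in advance instead of choosing between t and rank test from the data. This is good practice for a fixed plan; it does not correct a bias in size.

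The method is already implicit in the plan. The information time in the interim analysis section sums n·n/(n + n + 1) over strata, which is 12 times the null variance of the van Elteren statistic.

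The cost is one sentence and no new data. Sparse strata for rare events such as renal replacement therapy call for the exact stratified test. That test keeps most of the conservatism due to discreteness (null rejection 2.7 to 2.9% in the equal-strata runs), so it recovers only the part due to the strata.
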